#### Usual care

Concerning impairments in body functions and structures usual care physiotherapy goals are to prevent and treat impairments in range of motion, muscle tone, muscle mass, generalized and respiratory muscle strength, the cardiorespiratory system, and exercise capacity. Concerning impairments in activities, physiotherapy goals are to improve functional status, balance, transfers, and walking capacity. Active physiotherapy consists of progressive active exercises in bed or on a chair, active ergometer cycling, walking, active range of motion exercises, transfer training, balance training, active functional training exercises, and IMT [18].

The treatment plan for critically ill patients with at least Medical Research Council sum-score 2 (MRC 2) in the lower extremities will focus largely on progressive (guided) active and functional training. Passive physiotherapy is seldom applied since active physiotherapy interventions are preferred in responsive patients. Starting from MRC 3 in the lower extremities, treatment will also focus on standing up and walking.

Various exercise equipment is applied during physiotherapy treatment. Weights, elastic resistance bands, and computer games will be used to assist in active exercises. We will use walking frames, walkers, active lifts, and other aids to assist in training balance, transfers, and walking.

Usual care consists of one or multiple individual supervised physiotherapy sessions on a daily basis 7 days per week. The physiotherapist decides which exercises are administered based on the current (medical) status, the preference and tolerance of the patient at the time of the treatment session and available guidelines regarding evaluation of safety criteria and clinical observations [18]. These physiotherapy sessions will be performed by experienced ICU physiotherapists and will be continued on the regular wards after ICU discharge until hospital discharge or until pre-admission functional status is achieved and all treatment goals have been reached.

#### Main study endpoint

The main study endpoint is the number of days to functional ambulation of 3 or higher as measured with the FAC. The FAC categorizes patients according to basic motor skills necessary for functional ambulation [21]. FAC categories are rated as follows:

(0) The patient cannot walk, or needs help from two or more persons, (1) the patient needs firm continuous support from one person who helps carrying weight and with balance, (2) the patient needs continuous or intermittent support of one person to help with balance and coordination, (3) the patient requires verbal supervision or stand-by help from one person without physical contact, (4) the patient can walk independently on level ground, but requires help on stairs, slopes, or uneven surfaces, (5) the patient can walk independently anywhere.

The FAC will be assessed daily until hospital discharge by a researcher blinded to the intervention. Should a patient still receive BWSTT after transfer to the regular ward, the study intervention, and the blinded outcome assessment will be performed separately. If a patient is discharged to another hospital before the main study endpoint (FAC 3) is reached, the assessment of walking capacity will be continued until a FAC score of 3 has been reached.

#### Secondary endpoints

The secondary endpoints are walking distance as measured with the 2 Minutes Walking Test (2MWT) [22], muscle strength of upper and lower extremities as measured with the Medical Research Council sum-score (MRC sum-score) [19], perceived exertion after physiotherapy interventions as measured with the Rating of Perceived Exertion scale (RPE scale) [23], physical strain during physiotherapy interventions as measured by peak values of heart rate, mean arterial pressure, respiratory frequency and oxygen saturation, functional mobility as measured with the De Morton Mobility Index (DEMMI) [24, 25], duration of mechanical ventilation, ICU, and hospital length of stay, discharge destination, symptoms of post-traumatic stress as measured with the Posttraumatic Stress Disorder Checklist (PCL-5) [26] and patient satisfaction as measured with a 5-point Likert scale. (Serious) Adverse Events (S) AEs related to the study intervention will be recorded in accordance with good clinical practice guidelines and legislation. Physiotherapy intervention characteristics including numbers of staff and time needed, frequency and content of treatment and walking time, distance and support needed during BWSTT will be recorded for both groups. Outcomes will be assessed at different points in time as is shown in Fig. 2.

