#### Exclusion criteria

Exclusion criteria are; the presence of contraindications for physiotherapy according to the evidence statement for ICU physiotherapy [18] such as heart rate of < 40 or > 130 beats per minute, a recent myocardial ischemia or a mean arterial pressure (MAP) of < 60 or > 110 mmHg, surgical contraindications (i.e. instable fractures, craniotomy, open abdomen or thorax), insufficient knowledge of the Dutch language, inability to walk independently in the month prior to ICU admission, one or more amputated lower extremities, mental retardation and when death is imminent. Patients with neurological diseases and disorders as indication for ICU admission are excluded because underlying pathology may affect recovery of functional walking ability.

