**Fig. 1 Fig1:**
[figure not shown]
Schematic illustration of the BWST

A mobile treadmill with weight-bearing utility will be used for BWSTT (Fig. 1). The body weight-supported treadmill enables early ambulation in patients with insufficient motor control or muscle strength to fully bear weight. The treadmill has been developed in the Amsterdam UMC.

The intervention will be provided by trained physiotherapists. BWSTT is provided on a daily basis for 5 days per week (not during the weekend) in the ICU or medium-ICU (MICU) and the regular ward.

For each session, two physiotherapists are involved. Before the BWSTT, the patient is seated upright at the side of the bed and the harness is fitted. The treadmill is positioned at the bedside and the harness is fastened to the safety lines attached to the frame of the BWST to support bodyweight. One physiotherapist stands next to the BWST to adjust the amount of bodyweight support and to monitor vital functions at the bedside monitor. The second physiotherapist guides the patient and coordinates the intervention in terms of walking speed and distance depending on the walking capacity of the patient. The aim is to have the patient walk at a self-chosen comfortable walking speed. The intervention stops as the vital signs exceed the safety criteria [18], the patient indicates that he has reached his maximum load, or according to the clinical observation of the patient by the physiotherapist. After a period of recovery, if vital signs and perceived exertion return to pre-exercise levels, the physiotherapist may decide to continue BWSTT in consultation with patient and medical staff in order to reach a sufficient training load. This exercise can be repeated multiple times before the intervention is ended. When the intervention is ended the harness is removed while the patient is seated at the bedside, the patient will then be guided back to a supine position in bed.

After ICU discharge, BWSTT will be continued daily on the regular ward until the patient is able to ambulate with walking aid and minimal physical support for balance assistance (Functional Ambulation Categories [FAC] ≥ 2). Physiotherapy according to usual care will be provided from that point on until hospital discharge.

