#### Adverse events

(S) AEs potentially related to the study intervention, reported to, or observed by the study personnel will be documented in the source documents. For SAEs, this includes any untoward medical occurrence, event or effect related to the study intervention that at any dose is life-threatening, results in death, prolonged hospitalization, significant disability or incapacity and the occurrence of falls, wounds, dislocation of mechanical ventilation, and arterial lines. For each, potentially study-related (S) AE, the time of onset and the time when resolved, type, any action taken and intensity will be recorded in the case record form (CRF). Evaluation of outcome, seriousness, period, treatment, and the relationship with the study (causality) will be classified for each study related (S) AE. All study related (S) AEs of subjects being part of the analysis will be listed and described in the report.

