#### Statistical analysis

Sample size was calculated using data from previous studies where BWSTT [12] and usual care [24] was provided to critically ill patients in the Amsterdam UMC. Data of 35 patients were retrieved. On average, these patients reached the endpoint (≥ FAC 3) at day 15 after the inclusion criteria were met. In the sample data, we found a hazard ratio of 1.87 at 15 days in favor of BWSTT. All patients reached the endpoint within the study period. Given a type 1 error rate of 5% and a power of 0.8 the analysis resulted in a required sample size of 88 (44 + 44) patients before correction for attrition, assuming a 10% dropout rate. A check on sample size assumptions will be performed after inclusion of 40 participants as the dataset used for sample size to calculate was relatively small.

The primary objective of this study is to assess the effect of BWSTT in critically ill patients on time to functional ambulation as compared to usual care. For this, Kaplan-Meier analyses will be performed and comparisons between both groups will be made. For the primary analysis we will use intention to treat principles. Multiple imputation will be applied in cases where the primary outcome is missing. Cox regression analysis will be performed when imbalances between groups are found at baseline in age (mean difference ≥ 10%), muscle strength (MRC sum-score mean difference ≥ 10%), functional ambulation level (FAC mean difference > 1) and co-morbidities (Charlson Comorbidity Index [CCI] mean difference > 1) as they are potentially related to the primary outcome. Significance values are not considered when determining baseline differences.

The secondary objective of this study is to analyze between group differences of other patient relevant outcome measures for the evaluation of BWSTT. Patient characteristics and secondary study endpoints will be described using descriptive statistics according to their distribution. If the variables are normally distributed, they are expressed as mean and standard deviation (SD). Skewed variables are presented with medians and interquartile ranges (IQR). Between groups comparisons will be made using the appropriate tests according the variable type and distribution.

For this study, analysis will be performed using the software package R version 3.6.1.

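### The physical strain endpoint records the peak of oxygen saturation, which is the wrong direction and cannot show exertional desaturation

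*Protocol article*

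**What the plan says.** Secondary endpoints in the protocol article include "physical strain during physiotherapy interventions as measured by peak values of heart rate, mean arterial pressure, respiratory frequency and oxygen saturation". The item stands directly after perceived exertion on the RPE scale. No lowest value, change from rest or count of out-of-range readings is given for any of the four signs.

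Three other parts of the article deal with vital signs, none of them as part of this endpoint:

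- **Exclusion criteria** give examples of contraindications for physiotherapy, among them "heart rate of < 40 or > 130 beats per minute" and "a mean arterial pressure (MAP) of < 60 or > 110 mmHg". The examples include no saturation limit.
- **BWSTT intervention** assigns one physiotherapist to adjust the weight support and "to monitor vital functions at the bedside monitor". Walking stops when vital signs pass the cited safety criteria. It may resume after a pause if vital signs and perceived exertion are back at their pre-exercise level, and this can happen several times in a session.
- **Adverse events** provides for documenting events potentially related to the study intervention that are reported to or observed by study personnel.

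**The concern.** A summary statistic has to point in the direction in which the sign moves under strain. Heart rate and respiratory frequency rise with load, so their peak measures it. Saturation falls with exertional strain and is bounded above by 100%, so its peak describes the patient when least strained.

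If the case report form follows the text, the saturation component compares resting or recovered values between arms. Desaturation during treadmill walking could be more frequent or deeper than in usual care and this component would still show no difference. That matters because the Discussion calls for thorough evaluation of safety and efficacy before BWSTT enters usual care, and this item is the listed physiological measure taken during sessions.

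A lesser point concerns MAP. Its peak is a fair load measure, but it carries no information about a fall in pressure during a session.

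**Working it through.** The document states no figure for this endpoint, so there is none to reproduce. The check is on the definition, with a small illustration.

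**Inputs.** From the document: the summary is the peak, read as the maximum, for all four signs (Secondary endpoints); sessions may contain pauses in which vital signs return to the pre-exercise level (BWSTT intervention). Assumed: the readings below. They are illustrative and are not trial data.

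**Step 1: the definition.** For readings s1, …, sn in a session, the recorded value is max(s1, …, sn). If any resting or recovered reading r is included and the exercise reading e is below r, then max ≥ r whatever the value of e. The recorded value does not change with the depth of the fall r − e. Because the article allows recovery pauses within a session, a recovered reading will often fall inside the recording window.

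**Step 2: illustration for saturation and MAP.**

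| Sign | Calm session | Session with a fall | Peak (calm / fall) | Lowest (calm / fall) |
|---|---|---|---|---|
| Saturation, % | 96, 96, 95, 96 | 96, 90, 82, 95 | 96 / 96 | 95 / 82 |
| MAP, mmHg | 78, 85, 88, 80 | 78, 88, 52, 70 | 88 / 88 | 78 / 52 |

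The difference in peaks is 96 − 96 = 0 points for saturation and 88 − 88 = 0 mmHg for MAP. The difference in lowest values is 95 − 82 = 13 points and 78 − 52 = 26 mmHg.

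**Step 3: does this depend on the window?** Suppose only the two middle saturation readings were recorded, with rest and recovery left out. The peaks would be max(96, 95) = 96 and max(90, 82) = 90, a difference of 6 points, against 13 for the lowest values. A narrow window would let part of the fall through, but the maximum would still pick the reading least affected by strain.

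**Step 4: sign by sign.** For saturation the peak runs against the direction of strain, so the component is wrong as written. For heart rate and respiratory frequency it runs with the direction of load. For MAP it is acceptable for load and silent on a fall.

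**The case against.** **The endpoint measures load, not safety.** It is named physical strain and sits beside perceived exertion, so the peak is a natural choice. This stands for heart rate, respiratory frequency and MAP, and those peaks should be kept. It does not rescue saturation, which falls under load.

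**The two-sided limits in the Exclusion criteria.** A reader might infer that a peak of heart rate or MAP contradicts these limits, since it can show only an upper crossing. The document does not support that. The limits are examples of contraindications at entry and do not define strain. With no saturation limit among the examples, they also lend nothing to the main point.

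**Low values are handled elsewhere.** A reader might infer that desaturation or hypotension on a device without CE certification would go unseen. That too is unsupported. Bedside monitoring, the stopping of sessions on safety criteria, reporting of related adverse events and the DSMB's review of safety data all offer routes by which such events could surface. None is described as giving a per-session comparison of low values between arms, so the flaw in this component remains.

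**The article is a condensation.** The full protocol, the case report form and the assessment schedule in Fig. 2 are not shown, and *peak* may be shorthand for the most extreme value. That is possible, but nothing in the shown text says so. What is at issue is not an omitted detail: the article states the measure, and for saturation states it in the wrong direction.

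**No conclusion of equal strain is planned.** This is fair. Secondary endpoints receive descriptive statistics and between-group tests, and no non-inferiority claim on strain is made. The consequence is a component that cannot inform, not a false conclusion already built into the plan.

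**Conclusion.** The point holds for one of the four components. The peak of oxygen saturation is the wrong summary: it normally returns the resting or recovered value and cannot show exertional desaturation or a between-arm difference in it. For MAP there is only a limited gap, in that the peak cannot show a fall. The peaks of heart rate and respiratory frequency need no change.

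This rests on reading *peak* as the maximum and on a recording window that includes rest or recovery. With a narrower window the loss is partial. The size of the effect in the trial cannot be estimated, because the document gives no saturation or MAP data; the readings above show the mechanism only.

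The point does not show that the trial would miss such events altogether. The primary endpoint is time to FAC 3 or higher, and the sample size rests on pilot data in which "we found a hazard ratio of 1.87 at 15 days in favor of BWSTT". Neither uses the strain measure, so both are unaffected.

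**What to change.** 1. Define the saturation component as the lowest oxygen saturation during the session. Keep the peak for heart rate, respiratory frequency and MAP. If *peak* was meant as the most extreme value, say so and name the direction for each sign.
2. Where MAP is already being monitored, record the lowest MAP as a separate field beside the peak. Highs and lows should not share one field, because its group mean could not be interpreted.

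The first change is a matter of wording and one redefined field, at almost no cost. The second adds one field, available only where MAP is measured. The article describes the bedside monitor for BWSTT sessions but not for usual care, and both treatments continue on regular wards, so the number of sessions with a lowest MAP should be reported by arm. For sessions already completed, low values can be recovered only where monitor data were stored. No treatment or stopping rule changes.

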**Fig. 2 Fig2:**
[figure not shown]
Schedule of enrollment, interventions, and assessments (SPIRIT)

Other patient characteristic including age, gender, severity of the disease [27, 28], reason for admission, co-morbidity [29], pre-ICU functional ambulation, and the presence of drains and infusion lines will be recorded from the patient files.

#### Data storage and archiving

A Trial Master File containing all study documents will be compiled in accordance with GCP guidelines and the Dutch Medical Research Involving Human Subjects Act (WMO) and will be stored safely [30]. These documents will only be accessible by research staff directly involved in this study. Castor EDC (Amsterdam, The Netherlands) will be used as online database, we will use digital case report forms to collect and store data.

After the end of the study all documents will be archived for a period of 15 years.

All included patients are identified by a PIN. A list of PIN/name combinations will be securely stored by the head investigator.

A privacy impact analysis has been performed and approved by the Amsterdam UMC’s privacy officer in order to warrant confidentiality of privacy before, during, and after the trial.

#### Monitoring and Data Safety Monitoring Board

In this study a non-CE certified medical device (mobile treadmill) will be used. This study is classified as a moderate risk study by the Amsterdam UMC (AMC) local Ethics Committee and will be monitored by a certified monitor according to Amsterdam UMC monitoring policy. A Data Safety Monitoring Board (DSMB) has been installed consisting of an independent intensivist, epidemiologist, and a statistician. Specific tasks of the DSMB are to monitor safety data to guide recommendations for continuation of the study or early termination because of clear harm, to evaluate the overall conduct of the trial and to monitor sample size assumptions.

#### Adverse events

(S) AEs potentially related to the study intervention, reported to, or observed by the study personnel will be documented in the source documents. For SAEs, this includes any untoward medical occurrence, event or effect related to the study intervention that at any dose is life-threatening, results in death, prolonged hospitalization, significant disability or incapacity and the occurrence of falls, wounds, dislocation of mechanical ventilation, and arterial lines. For each, potentially study-related (S) AE, the time of onset and the time when resolved, type, any action taken and intensity will be recorded in the case record form (CRF). Evaluation of outcome, seriousness, period, treatment, and the relationship with the study (causality) will be classified for each study related (S) AE. All study related (S) AEs of subjects being part of the analysis will be listed and described in the report.

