## Discussion

BWSTT has shown to be an effective modality for ambulatory function in different rehabilitation populations with muscle weakness [12–14]. This might indicate that BWSTT could also benefit critically ill patients in their recovery to independent function ambulation. However, it has never been evaluated in critically ill patients. Early ambulation training in critically ill patients on the ICU supported by BWSTT can possibly facilitate and shorten the first time to ambulation and improve functional status at ICU and hospital discharge [12]. Another potential beneficial factor of BWSTT is that less time and staff are needed for ambulation training as a patient can stay at the bedside. Furthermore, BWSTT can provide a mental boost as making the first steps after or during critical illness can provide a patient with a more positive future perspective and more self-confidence, especially for those patients who have been at the ICU for an extended amount of time. Early ambulation training using BWSTT within a group of fragile critically ill patients should be evaluated thoroughly on safety and efficacy before implementing in usual care.

A possible limitation of the Steps to Recovery trial is blinding of group assignment for outcome assessors on the ICU. Assessments on the ICU cannot be blinded because having a blinded assessor assess all outcomes on the ICU would be too demanding for patients in addition to the interventions given. Despite the challenges in blinding outcome assessors on the ICU, it is important to note that it is expected that the primary outcome (time to independent ambulation) will be reached on the regular wards where blinded assessments are performed. Another possible limitation is the generalizability of these study results as we have only included a limited part of the ICU population and excluded neurological patients, albeit for a good reason as this underlying pathology may affect recovery of functional walking ability.

In summary, the Steps to Recovery trial is the first randomized controlled trial to evaluate the effects of BWSTT on recovery time to functional ambulation in critically ill patients. The results of this study will add to the knowledge of early rehabilitation and recovery of critically ill patients.

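### Adverse events are captured only if related, or potentially related, to the treadmill training, so as written they cannot be validly compared between the randomised arms

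*Protocol article*

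**What the plan says.** Four statements in the protocol article set the rule.

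- **Documentation** (Adverse events): "S) AEs potentially related to the study intervention, reported to, or observed by the study personnel will be documented in the source documents".
- **Definition of a serious event** (Adverse events): "any untoward medical occurrence, event or effect related to the study intervention that at any dose is life-threatening, results in death, prolonged hospitalization". Relatedness is part of the definition, even for death. The same sentence goes on to name falls, wounds, and dislocation of the ventilator connection or arterial lines.
- **Reporting** (Adverse events): "All study related (S) AEs of subjects being part of the analysis will be listed and described in the report".
- **Secondary endpoints**: "AEs related to the study intervention will be recorded in accordance with good clinical practice guidelines and legislation". Here the threshold is 'related', not 'potentially related'.

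The Main study endpoint section shows what 'study intervention' refers to: "Should a patient still receive BWSTT after transfer to the regular ward, the study intervention, and the blinded outcome assessment will be performed separately". According to the abstract, the control group receives usual-care physiotherapy only.

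The Monitoring section says that the treadmill is not CE certified. It asks the DSMB to use safety data in advising on continuation or "early termination because of clear harm". The Discussion says that this kind of training in fragile patients "should be evaluated thoroughly on safety and efficacy before implementing in usual care".

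**The concern.** A randomised safety comparison needs events to be captured in the same way in both arms. Here the entry condition is a link to something that only one arm receives. Usual care, as described, includes walking, transfer and balance training, so falls and line dislocations can happen in control sessions too. The rule does not require those to be written down.

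The filter also acts inside the BWSTT arm. Physiotherapists and participants know the allocation (Randomization and blinding), and an event regarded as due to critical illness need never enter the record. It cannot then be re-adjudicated.

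The resulting bias has no fixed direction. One-sided capture can make equal risks look like harm, and filtering in the BWSTT arm can hide real harm. At stake are the adverse-event evidence available to the DSMB for a non-certified device, and any comparative safety statement in the final report. The primary efficacy result is not affected.

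**Working it through.** No figure in the plan rests on this point, so there is none to reproduce. The check is a reading of the text followed by an illustration of size.

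**Reading, step by step**

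1. The documentation, definition and reporting sentences each carry a condition of being related, potentially related or study-related. No sentence provides for capture regardless of cause.
2. 'Study intervention' is used for BWSTT, and controls are not exposed to BWSTT. Read literally, a control-arm event cannot meet the condition.
3. The BWSTT arm also receives usual care. Events in its usual-care sessions face the same filter, so capture in that arm may be incomplete as well.
4. The Secondary endpoints section says that physiotherapy session characteristics (staff, time, frequency, content) are recorded for both groups. The adverse-event sentence just before it does not say so.
5. The two sections set different thresholds ('potentially related' and 'related').

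**Illustration of size**

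Inputs: 44 patients per arm (Statistical analysis). Assumed, because the article gives no rates: 6 patients with an event in each arm, so no true difference; no control events recorded; and between half and all of the BWSTT-arm events recorded.

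For k vs 0 events with equal arms, the two-sided Fisher exact p = 2 × C(44,k) / C(88,k).

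| Recorded | Calculation | p |
|---|---|---|
| 3 vs 0 (half captured) | 2 × 13,244 / 109,736 | 0.24 |
| 5 vs 0 | 2 × 1,086,008 / 39,175,752 | 0.055 |
| 6 vs 0 (all captured) | 2 × 7,059,052 / 541,931,236 | 0.026 |

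The true table in every row is 6 vs 6.

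The second calculation enumerates Fisher's test exactly at 44 per arm and the 5% level. It assumes the same true risk in both arms, half of BWSTT-arm events recorded, and no control events recorded.

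| True risk, both arms | Expected true events per arm | Expected recorded, BWSTT vs control | Chance of p < 0.05 |
|---|---|---|---|
| 10% | 4.4 | 2.2 vs 0 | 2% |
| 20% | 8.8 | 4.4 vs 0 | 27% |
| 30% | 13.2 | 6.6 vs 0 | 66% |
| 40% | 17.6 | 8.8 vs 0 | 90% |

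With full capture in both arms the chance is 2–3% throughout. At low event rates a spurious signal is therefore unlikely, and at higher rates it becomes likely. The opposite error, real harm judged unrelated and never logged, is not bounded by these figures.

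**The case against.** Several counter-arguments have force.

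- **The bar is low, and the wording could be read more broadly.** In the Adverse events section 'potentially related' is enough for entry, and causality is classified afterwards. That section also speaks of relationship with the study, and its list of falls, wounds and dislocations could be taken as predefined events outside the relatedness clause. A reader might infer that the control arm will have almost no events by definition. The text does not go that far: some control events might be recorded, but nothing promises it. This stands, and the ambiguity itself needs resolving.
- **No test is planned.** The Adverse events section plans to list and describe events. The p-values above show how a record could mislead; they do not predict a planned analysis, and 6 vs 0 is the worst case. This stands.
- **Other safety data are unfiltered.** Peak heart rate, arterial pressure, respiratory frequency and saturation during physiotherapy, length of stay and discharge destination carry no relatedness condition. A reader might infer that the whole safety comparison is lost, or that excess deaths would be invisible. Neither is supported. Daily FAC follow-up and discharge destination would bring many deaths to light, although all-cause death is not a named endpoint.
- **The DSMB may see more.** Its task refers to safety data without restriction, and its working documents are not shown. It would be too strong to say that it has no comparator. What can be said is that the stated rule does not supply one for adverse events.
- **The trial's aim is ambulation.** The call for thorough safety evaluation is a Discussion statement about what should precede implementation, not a study objective. This stands.
- **The article is condensed.** It defers to good clinical practice and legislation, and the full protocol is not shown. Missing detail would be no finding. A capture rule that the article states outright is different, and it can be judged as stated.

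**Conclusion.** The point holds for adverse events. Followed as written, the rule gives unequal capture between arms, and the resulting counts cannot support a between-arm safety conclusion. This rests on reading 'study intervention' as BWSTT, which the Main study endpoint section supports, and on the list of falls, wounds and dislocations falling under the relatedness condition, which is the more natural but not the only reading. That the filter is applied with knowledge of allocation is an inference from the unblinded treating staff; the article does not say who judges causality.

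The size cannot be fixed from the document. With 6 true events per arm and no control capture, the record would run from 3 vs 0 (p = 0.24) to 6 vs 0 (p = 0.026). Whether or not a false signal appears, the comparison is unreliable.

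**What to change.** 1. Reconcile the Secondary endpoints and Adverse events sections on one threshold, and state explicitly that it applies to both arms.
2. In both arms, over the same period and by the same method, record all-cause death, and every fall, wound, and ventilator or arterial-line dislocation during any physiotherapy session, regardless of judged cause.
3. Classify relatedness afterwards as a separate field, blinded to allocation where possible.
4. Give counts to the DSMB, and in the final report, by randomised arm with the number of sessions as denominator.

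The cost is a small CRF amendment and slightly more recording in control sessions; session data are already collected in both groups. Timing is the main drawback. Enrolment began in May 2018 and was to end in September 2020, and the article appeared in May 2020, so a late change would cover few patients prospectively. Earlier events would have to be retrieved from patient files where possible, and the change of capture rule reported.

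If the amendment is not made, the report should state that the adverse-event data describe BWSTT only and support no between-arm safety conclusion.
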